research plan

November 29, 2022 Ver.1

December 6, 2022 Ver.2

December 23, 2022 Ver.3

February 2, 2023 Ver.4

February 21, 2023 Ver.5

February 28, 2023 Ver.6

1. Title of Research

　　Verification of the effects of an intervention using the Sensory Room on sensory processing characteristics in healthy adults: a randomized controlled trial

2. Background of the study

In recent years, difficulties in social participation have become an issue for people with psychiatric disorders such as schizophrenia and autism spectrum disorder (ASD), with sensory processing disorder considered one of the causes^1)^. Sensory processing disorder refers to the process of perceiving all stimuli in the environment as visual, auditory, and other information, integrating the information in the brain, recognizing the situation, and connecting it to the next action. This is believed to result in hypersensitive reactions to environmental stimuli and misunderstanding of social signs such as facial expressions shown by others, as well as social withdrawal resulting from such reactions^2)^.

In clinical settings, interventions using sensory rooms that focus on sensory processing disorders are commonly used in Western countries. sensory rooms are rooms in which sensory stimuli can be modulated to the appropriate level, and their effects are said to include relaxation of the body and mind and the acquisition of self-control over sensory input^3)^. However, most of the reports are based on qualitative studies, and the evidence is insufficient to verify them.

Conventional psychiatric occupational therapy involves programs using a variety of occupational activities and exercise, such as handicrafts, reading, puzzles, and light exercise. Interventions using occupational activities are said to have a certain effect on improving mood and cognitive function^4)5)^. However, none of these interventions focus on the senses, and the difference in effectiveness between occupational activities and sensory interventions is not clear.

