In the field of neurophysiology, it has been shown that sensory processing disorders are associated with autonomic function and electroencephalography. Specifically, children with ASD have reduced parasympathetic function when exposed to sensory stimuli, resulting in a disturbance in the balance of autonomic function^6)^, and patients with schizophrenia have impaired cognitive processes such as paying attention to information detected after inputting sensory stimuli, as indicated by the event-related potentials (ERPs) of the electroencephalogram, N1, MMN (mismatch negativity), and P300^7)^. For parasympathetic function, we focused on respiratory sinus arrhythmia (RSA), which is a heart rate variability that is faster during inspiration and slower during expiration, reflecting vagal activity that fluctuates with respiration and is widely used as an indicator of pure parasympathetic function. It is widely used as an indicator of pure parasympathetic function^8)^.

Atypical sensory processing characteristics are also present in healthy individuals who have not been diagnosed with psychiatric disorders. In a study of healthy subjects, it was reported that latencies of P2 event-related potentials to large frequency changes in auditory stimuli were significantly longer in hypersensitive subjects than in nonsensitive subjects^9)^ and that hypersensitivity to sensory stimuli and the tendency to avoid sensory stimuli were associated with the amount of stress felt in daily life^10)^.

However, as far as we could find, there were no reports on the usefulness of the Sensory Room using physiological indices such as autonomic function or electroencephalogram (EEG) activity, regardless of the diagnosis of psychiatric disorders, and the effect of the Sensory Room at the biological response level has not been clarified.

3. Purpose and Significance of the Study

1. What are you trying to clarify?

The purpose of this study is to demonstrate the effectiveness of a sensory room intervention (hereafter referred to as SRI) focused on sensory processing characteristics in healthy subjects through changes in biological indicators such as autonomic indices and electroencephalogram, as well as subjective mood state and cognitive function. This will allow us to clarify the usefulness of the intervention focusing on sensory processing characteristics through basic research.

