The research question is: Does a sensory room intervention increase parasympathetic activity and EEG amplitude, and improve mood state and cognitive function compared to static activity in healthy adults?

1. What is the medical and social significance?

The uniqueness of this study lies in demonstrating the therapeutic effects of the Sensory Room through changes in physiological indices, such as autonomic nervous system function and EEG activity, as well as cognitive function. We believe that demonstrating the usefulness of the Sensory Room in healthy subjects through objective measures and improved cognitive function will greatly contribute to proposing a new treatment method for people with psychiatric disorders, of which a high percentage are believed to suffer from sensory processing disorders. In the future, the effectiveness of the Sensory Room is expected to be widely publicized, leading to its installation in hospitals, educational institutions, and workplaces, and to the improvement of mental health care and work efficiency for people with developmental disabilities and mental disorders as well as healthy people. In addition, the role of occupational therapists and the usefulness of occupational therapy in making the above contributions will be clarified.

4. How to select research subjects

1. setting

We will collect the subjects by posting information and distributing flyers (Ref.1) to healthy adults, undergraduate and graduate students living in the community, and others who inquire about this research, explaining the contents of this research orally and in writing.

1. Eligibility Criteria

　　Persons who meet all of the following selection criteria and none of the exclusion criteria will be enrolled as eligible.

Selection Criteria

1. The patient must be between 18 and 65 years of age at the time of registration.
2. Written consent to participate in the research has been obtained from the research subjects themselves.
3. Total score of 1 or more points on the JSI-mini (Japanese Sensory Inventory mini) (Ref.2)

The rationale for setting the age of the subjects (a) is that the subjects of this study are adults and that the decline in physical and mental functions due to old age may affect the results of the study. The reason for (c) was to target people who have some characteristics of sensory processing in their daily lives, which is the intervention target of this study.

Exclusion Criteria

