Persons who fall into any of the following categories shall not be used as research subjects.

1. Complications of cardiac disease.
2. Cardiac pacemaker users
3. History of epilepsy
4. Visual acuity (correctable) less than 0.7 in both eyes
5. Air conduction hearing greater than 30㏈.
6. There is tactile hypoesthesia (unable to perceive Semmes-Weinstein monofilament no. 2.83)
7. Perceived significant taste and olfactory abnormalities
8. History of any other visual or hearing impairment, language comprehension disorder, mental disorder, or motor dysfunction that would interfere with the performance of the research task.

The reasons for setting (a) and (b) are because they may affect autonomic measurements and (c) because they may affect electroencephalography measurements. The reason for (d) through (g) is to exclude people with functional abnormalities in the sensory organs to be evaluated and intervened in this study.

Suspension Criteria

1. When the research subject wishes to discontinue
2. When it is deemed appropriate to discontinue other activities.

3) Number of research subjects and rationale for setting the number of research subjects

The target number of patients for this study is 58, consisting of 29 in the intervention group and 29 in the control group.

Regarding the rationale for the setting, this study will conduct a two-group comparison (unpaired t-test, one-tailed) of the intervention and control groups for changes in the parasympathetic index (RSA: respiratory sinus arrhythmia) before and after the intervention as the main outcome. Using G*Power 3.1.9.2 and referring to previous studies^11)12)^ that utilized RSA, the effect size was set to 0.7, with an alpha error of 0.05 and a beta error of 0.20, resulting in a total sample size of 52 participants. In addition, considering the possibility of approximately 10% dropout, approximately 58 subjects will be needed for the study. 58 subjects will be randomly divided into 29 in the SRI group and 29 in the control group.

The number of subjects in the previous study^6)13)^, which investigated parasympathetic indices and sensory processing characteristics in children with ASD and normal children, was 50 and 83, respectively, and we believe that the above number of subjects is generally appropriate.

5. Method of the study and the scientific rationale for the study

1) Design

□ Intervention study

Phase of study: Exploratory study

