Method of comparison: Before/after comparison/parallel group comparison

Method of allocation of intervention: Randomization

Blinding of evaluators: Blinding of only the researcher in charge of statistical analysis.

Therefore, this study is a randomized controlled trial.

2) Method

Those who are willing to participate in the study, agree to participate after receiving a thorough oral and written explanation from the investigator, and meet the eligibility criteria will be enrolled as study subjects. Using an allocation chart, the study administrator will randomly assign the subjects to the SRI group or the control group and implement the intervention. Afterwards, only the subject's ID and data will be sent to the co-researcher in charge of statistical analysis, who will conduct the analysis. In this way, blinding the researcher in charge of statistical analysis minimizes bias and ensures appropriate results.

The flow of implementation is shown in Figure 1. The study consists of six phases: (a) preliminary investigation (screening), (b) initial evaluation, (c) evaluation immediately before the intervention, (d) intervention, (e) evaluation immediately after the intervention, and (f) final evaluation. Each phase is described below. All surveys, evaluations, and interventions will be conducted at Human Health Science, Graduate School of Medicine, Kyoto University.

[figure not shown]

Figure 1: Flow of Implementation

1. Preliminary investigation (screening)

The main purposes of this survey are to screen subjects who are not suitable for the study and to evaluate their psychiatric disorders and sensory processing characteristics. The items measured were (1) basic information of the subjects, (2) medical information, (3) JSI-mini (Japanese Sensory Inventory mini), (4) Autism spectrum Quotient (AQ), (5) Schizotypal Personality Questionnaire (SPQ), and (6) the Japanese Adolescent/Adult Sensory Profile (A/ASP) (see "3) Observation Items and Schedule"). If the eligibility criteria are not met, the subjects will be asked to refrain from further participation in the study, and the experiment will be terminated with an honorarium, based on the time spent in the preliminary investigation. After enrollment of study subjects who meet the eligibility criteria, the subjects will be randomly assigned to two groups, the SRI group and the control group, and will be blinded to the assigned researcher (in charge of statistical analysis) until the end of the analysis.

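### Exclusion 8, on its natural reading, leaves people with a diagnosed mental disorder eligible if they can do the task, although the trial's question is about healthy adults

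*Protocol*

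**What the plan says.** The title is "Verification of the effects of an intervention using the Sensory Room on sensory processing characteristics in healthy adults: a randomized controlled trial". The purpose in section 3 is likewise set in healthy subjects, and the research question asks whether the intervention will, among other things, "improve mood state and cognitive function compared to static activity in healthy adults". Section 2 (Background) shows what the authors mean by healthy: "Atypical sensory processing characteristics are also present in healthy individuals who have not been diagnosed with psychiatric disorders".

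Section 4 (Eligibility Criteria) makes the lists decisive: "Persons who meet all of the following selection criteria and none of the exclusion criteria will be enrolled as eligible". The three selection criteria are age 18 to 65, written consent, and a JSI-mini total of at least 1. Among the exclusions, only item 8 mentions mental disorder. Besides past problems with sight or hearing that the earlier items do not cover, it names "language comprehension disorder, mental disorder, or motor dysfunction that would interfere with the performance of the research task". The protocol gives reasons for items (a) to (g) and none for this last item.

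Section 5, under the preliminary investigation, says that screening is meant "to screen subjects who are not suitable for the study and to evaluate their psychiatric disorders and sensory processing characteristics". Medical history, AQ and SPQ are collected there.

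**The concern.** The rule that should define a healthy sample depends on whether a disorder gets in the way of the task. It does not depend on whether the disorder exists. If the rule is applied as it most naturally reads, the trial may enrol people who are not healthy in the protocol's own sense, and its intended inference about healthy adults would not describe everyone in it.

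Three uses of the data are exposed:

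- **The main inference.** The Background says that "children with ASD have reduced parasympathetic function when exposed to sensory stimuli, resulting in a disturbance in the balance of autonomic function", and that patients with schizophrenia show impaired N1, MMN and P300. RSA under sensory stimulation is the primary outcome, and EEG amplitude is a secondary one.
- **The trait correlations.** AQ, SPQ and A/ASP scores are to be correlated with RSA and with changes in RSA, EEG amplitude and POMS2. Diagnosed subjects may sit at the extremes of these scales.
- **Later use as controls.** Section 5 (Initial assessment) intends the cognitive data as possible comparison data for later studies of people with mental disorders. Diagnosed subjects would blur that comparison.

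**Working it through.** The check is mainly one of reading. Four questions settle it.

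1. **Does any selection criterion require good health or no diagnosis?** No. Age, consent and the JSI-mini score are the only three.

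2. **Does item 8 exclude a diagnosis as such?** There are two ways to parse it.
   - *The condition governs the whole list.* Mental disorder excludes only if it would interfere with the task.
   - *The condition attaches only to motor dysfunction.* Any history of mental disorder then excludes, but so does any past visual or hearing impairment, however slight. That is hard to square with items 4 and 5, which set explicit thresholds for vision and hearing.

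   The first parse is the more natural. If the second was intended, the text is still unclear on the point that defines the population.

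3. **Does anything else close the gap?**
   - Screening says that it evaluates psychiatric disorders, but no finding is tied to exclusion.
   - The AQ cut-off of 33, given in section 5 3), has no stated consequence for eligibility.
   - Recruitment in section 4 is addressed to healthy adults, but also to "undergraduate and graduate students living in the community, and others who inquire about this research", and it is not a criterion.

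4. **Is the treatment of mental disorder consistent with the other exclusions?** Cardiac disease and pacemakers are excluded without condition because they may affect the autonomic readings, and epilepsy because it may affect the EEG. The Background describes disturbances in the same two domains for ASD (in children) and schizophrenia, yet mental disorder carries a condition about task performance.

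**Sample size, for completeness.** Inputs from section 4 3): effect size 0.7, one-tailed alpha 0.05, beta 0.20, equal arms, about 10% dropout.

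- With 26 per arm, the noncentrality parameter is 0.7 × √(26/2) = 2.52 on 50 degrees of freedom. Power is 0.801, which gives the stated total of 52.
- 52 / 0.90 = 57.8, rounded up to the stated 58.

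Both figures reproduce. Tightening item 8 changes neither.

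The size of the problem itself has no calculation. The document gives no share of diagnosed people among those likely to enrol, and no figure for how their response to the intervention would differ.

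**The case against.** The strongest reply is that the intent is clear. Recruitment is addressed to healthy adults and students, and screening is meant both to remove unsuitable people and to assess psychiatric disorders. Section 16 treats high AQ or SPQ scores as tendencies that might come to light, which suits people presumed undiagnosed. Item 8 can also be parsed so that any mental disorder excludes. This supports the view that the authors meant to exclude diagnosed people. It does not put that rule into the criteria, which alone decide enrolment.

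A second reply is that the task is demanding. It includes six sensory stimuli, sustained auditory stimulation, a cognitive battery and up to 2.5 hours a day, partly in a closed room under observation. An investigator might well judge that a given disorder interferes. That is fair, and it would be wrong to say that every stable person with a diagnosis could do it all. But exclusion then rests on case-by-case judgement.

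A third reply is that the evidence in the Background is narrow. It covers children with ASD and patients with schizophrenia, while this trial enrols adults, and it does not say that depression or anxiety alters these readouts. This stands, and the point should not be extended to those conditions.

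A reader might go further and infer a biased treatment comparison or a loss of power. The documents support neither. Allocation is randomised and the primary analysis compares change between arms, so diagnosed subjects would not favour one arm systematically. A power loss would need an assumed share of subjects who do not respond. An altered baseline or reactivity is not the same as no response to the intervention, and section 3 expects the approach to help people with psychiatric disorders, so even the direction is open.

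**Conclusion.** The point holds as a mismatch between the eligibility text and the stated population. On its natural reading, item 8 admits diagnosed people who can do the task, and no other criterion stops them. On the alternative parse the item is still ambiguous where it needs to be plain.

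What is at stake is who the result describes, how far it generalises, whether a few extreme subjects could sway the AQ, SPQ and A/ASP correlations, and how clean the cognitive data would be as a comparison set. The correlations are secondary, and section 5 labels the study exploratory, which limits the weight of that part.

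The conclusion rests on the wording alone. It does not assume that any diagnosed person has enrolled or will enrol, and no number can be put on the effect from this document.

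**What to change.** Split item 8 into two exclusions:

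- a history of diagnosed mental disorder, whether or not it interferes with the task;
- a history of any other visual, hearing, language-comprehension or motor problem, with the interference condition kept.

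Add a one-line reason, as is done for items (a) to (g). Apply the first part from the past and current medical history that screening already records. AQ and SPQ can remain continuous trait measures with no eligibility cut-off. There is no need to extend the rule to medication: that goes beyond the defect, and the screening items do not list medication.

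If diagnosed subjects are already enrolled, report the primary result with and without them.

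The cost is a short amendment, which section 18 sends to the ethics committee, and a few more screen failures. Each failure uses a 30-minute preliminary survey and the 500-yen honorarium already provided for. With 58 subjects to enrol over four years, that should be manageable. The sample size does not change.

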After the 30-minute intervention, a post-intervention evaluation was conducted. The evaluation items consist of (1) RSA measurement during the Sensory Challenge Protocol (SCP), (2) EEG measurement, and (3) Profile of Mood States 2nd Edition (POMS2), the same as the evaluation immediately before the intervention (see "3) Observation Items and Schedule"). The order of the procedures is RSA measurement, EEG measurement, and POMS2, in that order. The time required is approximately 60 minutes. We will examine how the intervention changes the subjects' autonomic nervous system function, EEG waveform trends, and subjective mood state in the intervention and control groups, respectively.

1. Final Evaluation

The day after the immediate post-intervention evaluation, the final evaluation will be conducted. The final evaluation will be conducted using the CAB (1) conducted in the initial evaluation (see "3) Observation Items and Schedule"). The time required is approximately 30 minutes. We will examine how the intervention changed the cognitive function of the subjects in the intervention group and the control group.

3) Observation, inspection, investigation, and reporting items and schedule

- Measurement item, measurement method, person or organization

The measurement items and methods are described below. All measurements are performed by the researcher.

1. Items to be conducted in the preliminary investigation

The following will be heard and evaluated. The time required is 30 minutes.

1. Basic information of the subjects (age, gender, educational and occupational history, handedness, intellectual function) (Ref. 3): The Japanese version of the FLANDERS Handedness Test (Ref. 4) is used to assess handedness, and the JART (Japanese Adult Reading Test) (Ref. 5) to assess intellectual function.
2. Medical information (history, current medical history, visual acuity, hearing, touch, taste, and smell) (Ref. 3): Visual acuity was assessed using the International Standardized Visual Acuity Test at 5 m, hearing using the Mimi Hearing Test, and touch using the Semmes-Weinstein monofilament.
3. JSI-mini (Japanese Sensory Inventory mini) (Ref. 2): A simplified version of the JSI-R (Japanese Sensory Inventory Revised), with 20 self-administered items. It is a simple way to grasp the tendency to receive sensory stimuli.

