The experimental flow is shown in Figure 2. The evaluation and intervention will be conducted over three days: on the first day, after explanation and consent, a preliminary survey and initial evaluation will be conducted; on the second day, the evaluation immediately before the intervention, the intervention, and the evaluation immediately after the intervention will be conducted; and on the third day, the final evaluation will be conducted. Each evaluation item will be conducted with appropriate breaks in between.

[figure not shown]

Figure 2: Measurement schedule

4) Summary of analysis

- - Primary Endpoint

(a) Differences in the variability of RSA values due to sensory stimulation of SCP before and after the intervention.

- - Secondary endpoint

(a) EEG amplitude differences before and after intervention, (b) POMS2 score differences before and after intervention, (c) CAB score differences at initial and final assessment, (d) correlation between AQ scores and RSA values, (e) correlation between SPQ scores and RSA values, (f) correlation between A/ASP scores and RSA values, (g) power spectrum by EEG band during intervention, (h) RSA power spectrum of each EEG band, (h) RSA during intervention

- - Main Analysis Methods

The statistical significance level is set at p < 0.05. A one-tailed test is used.

Basic information, medical information, and observation records during the use of the sensory room were compiled as descriptive statistics: RSA values were calculated as the difference between the SCP resting period and the mean value during each sensory stimulus; EEG amplitudes were obtained by subtracting the standard stimulus waveform from the deviant stimulus waveform of the presented task to obtain the amplitude of the positive or negative component during latencies of approximately 200 to 400 ms. The EEG amplitude is obtained by subtracting the standard stimulus waveform from the deviant stimulus waveform of the presented task.

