The experiment should be conducted while inserting rest breaks as appropriate, paying attention to research subject’s level of fatigue. During the experiment, the examiner should call out to the subject as necessary, while carefully observing the subject so that the subject does not become excessively fatigued. Only occupational therapists are to perform measurements and interventions. In the unlikely event of deterioration of physical condition or excessive psychosomatic stress, the measurement will be stopped immediately. In such cases, vital measurements should be taken first, and the experiment should be stopped if the pulse rate is 120/min or higher, diastolic blood pressure is 120 mmHg or higher, or systolic blood pressure is 200 mmHg or higher, in accordance with the rehabilitation implementation criteria. Even if there is no abnormality in the vital signs, the experiment will be terminated and the subject will be excluded from the study if there is concern that their physical condition will deteriorate further due to the continuation of the experiment, based on the subject's strong sense of burden, facial expression, respiration, sweating, and so on. If the subject's sense of strain is expected to recover after a few minutes of rest, we will resume the measurement after about 5 minutes of rest, while listening to the subject's wishes. The subject should be informed that he/she has the right to refuse to continue the study, and an environment in which he/she can communicate with the subject should be maintained at all times during the measurement and intervention.

10. Method of storage and disposal of samples and information

- 1. Retention period of information, etc.

Retain the paper for 10 years after publication.

- 1. Methods of storing information, etc. (measures to prevent leakage, mixing, theft, loss, etc.)

All data analysis, etc., will be performed within the Department of Human Health Sciences, Graduate School of Medicine. A computer for research use will be purchased in the laboratory and used without Internet access to prevent leakage to the outside and loss of data. In addition, passwords will be applied to the computers to prevent theft or loss of data.

- 1. If disposed of after the storage period, the method of disposal

After the retention period ends or when consent is withdrawn, personal information and personal data are destroyed by shredding paper media or by completely deleting electronic media.

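### Only the statistical analyst is blinded, and the protocol does not place the derivation of RSA (primary) and EEG amplitude (secondary) behind that blind

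*Protocol*

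**What the plan says.** - **Who is blinded.** Section 5. 1) Design: "Blinding of evaluators: Blinding of only the researcher in charge of statistical analysis".
- **What reaches that person, and when.** Section 5. 2) Method, after describing assignment and intervention: "Afterwards, only the subject's ID and data will be sent to the co-researcher in charge of statistical analysis, who will conduct the analysis". Whether data here means raw recordings or derived values is not stated.
- **The benefit claimed.** The same section adds: "In this way, blinding the researcher in charge of statistical analysis minimizes bias and ensures appropriate results".
- **Who measures.** Section 5. 3): "All measurements are performed by the researcher". Section 9. 4): "Only occupational therapists are to perform measurements and interventions".
- **When the arm is assigned.** Section 5. 2) describes allocation under the preliminary investigation, once eligibility is confirmed. The RSA and EEG recordings before and after the intervention are made on the second day, so all of them follow allocation. Allocation is concealed from the statistical analyst alone.
- **How values are derived.** Section 5. 4), under the main analysis methods, defines RSA as the resting value compared with the mean during each stimulus. For EEG it uses the deviant-minus-standard waveform "to obtain the amplitude of the positive or negative component during latencies of approximately 200 to 400 ms". No person is named for either step.
- **Who analyses.** Section 5. 2) says the blinded co-researcher. Section 8. 2) says the principal investigator, working on ID-numbered data. Section 17. 2) gives the researchers who conduct the study an analysis role. Section 17. 5) lists separate staff for statistics and data management.

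**The concern.** In a trial with physiological endpoints, blinding has to cover three steps: recording the signal, turning the signal into a number, and testing the numbers. The protocol blinds the third step explicitly and leaves the first unblinded. On the second it is silent.

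The second step can be protected even when the sessions cannot, because recordings can be scored later by someone who does not know the arm. If it is left open, a person who ran the sessions may decide which stretches of pulse wave or EEG to keep and which component to measure. A small lean in those decisions would go straight into the change scores and so into the difference between arms. The planned test is one-tailed, so a lean favouring the sensory room arm acts in the direction that can produce a significant result.

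The trial's stated contribution is evidence from objective measures. Readers will give weight to the sentence that bias is minimised, and the procedure as written does not support that sentence for the steps before the test.

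**Working it through.** **1. Does the blind cover derivation?**

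| Step | What the protocol fixes | Inside the blind? |
|---|---|---|
| Recording RSA and EEG | The researcher; occupational therapists only (5. 3, 9. 4) | No |
| Artefact handling; waveform to RSA or EEG value | Definitions in 5. 4); no person named | Not stated |
| Group comparison | Blinded co-researcher (5. 2); but principal investigator in 8. 2) and an analysis role for conducting researchers in 17. 2) | Yes under 5. 2); unclear once 8. 2) and 17. 2) are read with it |

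The middle row can be read two ways. Because 5. 4) describes derivation under analysis methods, it may belong to the blinded co-researcher. Because 8. 2) and 17. 2) give analysis to people who manage or conduct the study, it may belong to staff outside the blind. The text does not settle this, so blinded derivation is not secured.

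The ID numbering in 8. 2) does not settle it either. It is a privacy measure that replaces names, and the protocol does not say that it hides the arm from people who ran the sessions.

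**2. The plan's own sample size.**
Inputs from section 4. 3): effect size 0.7, one-tailed alpha 0.05, beta 0.20, equal arms, about 10% dropout.

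Power = P(T > t(0.95; 2n − 2)), where T is noncentral t with 2n − 2 degrees of freedom and noncentrality d·√(n/2).

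- n = 25 per arm: power 0.787
- n = 26 per arm: noncentrality 0.7 × √13 = 2.52, power 0.801

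This gives 26 per arm, 52 in total. Allowing for dropout, 52 / 0.90 = 57.8, rounded up to 58. Both stated figures reproduce, and nothing in this point changes them.

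**3. Illustration of what a bias would do.**
Assumption, not in the documents: there is no true effect, but recording or scoring shifts the mean RSA change by s SD in favour of the sensory room arm. The same formula applies with s in place of d. For s = 0.1 the noncentrality is 0.1 × √13 = 0.36 at 26 per arm and 0.1 × √14.5 = 0.38 at 29 per arm.

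| Assumed shift s | 26 per arm | 29 per arm |
|---|---|---|
| 0 | 5.0% | 5.0% |
| 0.1 SD | 9.9% | 10.2% |
| 0.2 SD | 17.5% | 18.6% |
| 0.3 SD | 28.2% | 30.3% |

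The table shows sensitivity to a bias if one exists. It is not evidence that one exists, or of its size or direction.

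**The case against.** The strongest reply is that a reader might infer that RSA and EEG values are in fact scored by arm-aware staff before the blinded step, and the documents do not say so. The statements in 5. 3) and 9. 4) concern taking measurements. Derivation appears under analysis methods, and 5. 2) keeps the analyst blinded until the analysis ends. On that reading, derivation is already blinded. This reply stands against the stronger inference. It does not show that derivation is behind the blind, and 8. 2) and 17. 2) point the other way.

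A reader might also infer that the protocol leaves the scoring of the primary endpoint to discretion. It does not say that. The open wording on polarity and window concerns EEG amplitude, which is secondary; for RSA, 5. 4) gives an arithmetic rule. Detailed artefact rules may properly sit in an analysis plan that is not shown, so their absence is no fault here. The point concerns who is masked when such rules are applied, which is a design feature that this protocol chose to state.

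Three further replies have weight:

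- The protocol is open that blinding covers only the analyst, and it calls the study exploratory. That is fair, but it does not justify the claim that bias is minimised.
- The false-positive figures rest on an assumed shift and could be attached to any trial with unblinded staff. Agreed; they are illustrations.
- A scorer who knows only whether a file is before or after the intervention, and treats both arms alike, does not thereby favour either arm. Agreed; hiding the time point is optional.

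**Conclusion.** The concern holds in a limited form. Three things follow from the text: blinding is confined to the statistical analyst; RSA and EEG are recorded by unblinded staff from the group that also delivers the intervention; and the protocol does not secure blinded derivation of the primary RSA values or the secondary EEG amplitudes. Sections 5. 2), 8. 2) and 17. 2) also differ on who analyses. It is therefore possible, though not established, that values are derived with knowledge of the arm. The sentence that this blinding minimises bias and ensures appropriate results is overstated, because masking the final test cannot undo bias introduced earlier.

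No size can be put on the bias from the documents. The sample size is unaffected. This is a cheap improvement, not a flaw that invalidates the design.

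**What to change.** In sections 5. 1) and 5. 2), state that:

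1. The co-researchers already named for statistics and data management recode the pulse-wave files from the Sensory Challenge Protocol and the oddball EEG files so that the arm is hidden from whoever scores them. Since session staff may recognise a subject ID, the code should replace the ID as well. Hiding the time point is optional.
2. Artefact rejection, RSA derivation and EEG component measurement are completed and locked on the coded files before the code is opened.
3. Subjects and session staff remain unblinded. This replaces the sentence claiming that bias is minimised.

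Reconcile sections 5. 2), 8. 2) and 17. 2) so that one account says who derives the values and who runs the comparison.

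Suggested replacement wording: *Subjects and the staff who run the sessions are not blinded. RSA and EEG values are derived and locked on coded recordings that conceal the assigned arm; the statistical analyst is also blinded. This limits bias in scoring and analysis but not in the conduct of the sessions.*

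Cost: a file-coding and key-keeping task for the data-management co-researchers, a few sentences of protocol text, and the ethics committee application that section 18 requires for any revision. Scoring has to wait until files are coded. No additional subjects or measurements are needed. The change cannot remove bias arising while the recordings are made, and the revised text should say so.
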